### Treatment and assessment schedules

The study period will run for 8 consecutive weeks from gestation week 24 to the end of week 31 (Fig. 1). At baseline, age, gestational age, number of previous pregnancies and/or births, relationship status and/or quality, education, employment status and country of birth will be collected, along with depression-related clinical data, including medical diagnoses, entry EPDS score, age of onset and length of index episode, number and severity of past depressive episodes, length and severity of current episode, family history of depression and current medication and/or psychotherapy use. Collected data will be de-identified and securely stored at the NICM.

**Fig. 1 Fig1:**
[figure not shown]
Pragmatic randomised controlled trial treatment flowchart. *EPDS* Edinburgh Postnatal Depression Scale, *G* gestational week, *DASS-21* 21-item Depression Anxiety and Stress Scale, *WHO-QoL-26* 26-item World Health Organisation Quality of Life Scale, *K6* Kessler 6 instrument, *PMR* progressive muscle relaxation, *BaM-13* 13-item Being a Mother Scale

### Safety monitoring

Owing to the morbidity of this population, women will undergo a weekly psychological assessment with the Kessler 6 (K6) instrument [110], either during the weekly session (intervention groups) or by telephone (usual care). If notable worsening or a ‘cut-off’ score is reached, immediate referral will be made to hospital antenatal mental health services. Any adverse events arising from the acupuncture intervention will be documented and reported to Western Sydney University and the South West Sydney Local Health District, and prevalence will be calculated. Such events are reportedly rare (occurring approximately 1.3 times every 1000 treatments) and generally of a mild [111, 112] to moderate nature [112]. However, if such events do occur, participants will be reminded of their right to withdraw from the study at any time.

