## Abstract

**Background:**

Depressed pregnant women face difficulty navigating a course between the potentially serious consequences of leaving depression untreated and significant limitations associated with conventional therapies, such as foetal toxicity and teratogenicity. Preliminary evidence is suggestive that acupuncture may provide a safe and effective alternative treatment option for antenatal depression; however, additional research is required. The purpose of this study is to further investigate this treatment possibility, with an additional examination of a potential biomechanistic acupuncture effect.

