As preliminary evidence is suggestive that acupuncture may be beneficial in reducing the severity of antenatal depression and may exert a regulatory effect upon the oxytocinergic system, additional research is warranted to determine whether acupuncture is a viable alternative therapeutic option. The aim of this study is to conduct an RCT to examine the hypotheses that acupuncture, compared with an attention comparator or usual care, reduces the severity and duration of antenatal depression, stress and anxiety; decreases adverse maternal and infant outcomes; improves maternal quality of life and infant bonding; and positively regulates OT and OTR expression.

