### Interventions

In the first session, a full case history will be taken and a traditional Chinese medicine (TCM) and meridian therapy diagnosis will be made. This will also occur for the usual care group upon trial entry. The intervention groups will then receive weekly 1-h treatments over the 8-week period. At the end of each session, 5 minutes will be spent gaining feedback regarding the session. Treatments will be conducted in the antenatal clinics of either hospital or at the NICM.

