### Outcome measures

Data and samples will be collected at various time points, including baseline, mid-intervention (week 4), end of intervention (week 8), birthing and hospital discharge (medical records) and 6 weeks post-natally. All questionnaires will be self-administered and collected by the principal investigator. The primary outcome endpoint, reduction in depression severity, will be assessed at baseline, at 4 and 8 weeks from trial entry and at 6 weeks post-natally via the EPDS, an extensively validated, clinically sensitive [138], 10-item self-report questionnaire. Additional secondary outcome endpoints will also be examined as follows :At the same time points as the EPDS, reduction in stress and anxiety will be monitored with the 21-item Depression Anxiety and Stress Scale (DASS-21) [139] and improvement to quality of life will be evaluated using the 26-item World Health Organisation Quality of Life Scale (WHO-QoL-26,) [140]. The DASS-21 is a short form of the clinically validated [141] and cross-culturally reliable [142] self-report measure of emotional states of stress and anxiety. The WHO-QoL-26 [140] is also an abbreviated form of this discriminant, content valid, internally consistent and reliable self-report measure for overall quality of life.Adjustment to parenting and maternal-infant bonding will be evaluated at 6 weeks post-natally via the 13-item Being a Mother Scale (BaM-13) [143]. The BaM-13 is a clinically discriminating, reliable and valid self-report tool specifically designed to enable early assessment of women’s experiences of motherhood.Maternal-infant outcomes such as gestational diabetes, mode of delivery, method of pain relief, labour augmentation, post-partum haemorrhage, breastfeeding level and duration, gestational age at delivery, birth weight, 1- and 5-minute Apgar scores, neonatal intensive care unit admission and need and reason for resuscitation and or intensive care will be assessed at delivery, discharge and 6 weeks post-natally.Salivary OT levels will be determined using saliva specimens collected by the principal investigator at baseline and at 4 and 8 weeks from trial entry. Leucocyte OTR messenger RNA (mRNA) expression will be assessed using blood collected by phlebotomists at local pathology centres at baseline and 8 weeks from trial entry.

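### The only stated adverse-event rule covers events attributed to acupuncture, so non-psychological events between trial entry and birth are not captured alike in the three arms

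*Protocol article*

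**What the plan says.** The Safety monitoring section of the protocol article states one adverse-event rule: "Any adverse events arising from the acupuncture intervention will be documented and reported to Western Sydney University" (and to the local health district), "and prevalence will be calculated". It describes such events as rare, "occurring approximately 1.3 times every 1000 treatments". No section gives a matching rule for the PMR or usual care arms.

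Other safety-relevant data are planned without restriction to one arm:
- **K6 (Safety monitoring).** It is taken every week in all three groups, at the session or by telephone, with referral if a woman worsens notably or reaches a cut-off.
- **EPDS and DASS-21 (Outcome measures).** They are collected at baseline, weeks 4 and 8, and 6 weeks post-natally. Statistical analysis plans between-group comparisons of depression, stress and anxiety.
- **Maternal-infant outcomes (Outcome measures).** The list opens "Maternal-infant outcomes such as gestational diabetes, mode of delivery, method of pain relief, labour augmentation, post-partum haemorrhage" and goes on to gestational age at delivery, birth weight, Apgar scores, neonatal intensive care admission and resuscitation.

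Under Interventions, "At the end of each session, 5 minutes will be spent gaining feedback regarding the session". That applies to acupuncture and PMR sessions and is not described as adverse-event collection.

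The Abstract says that preliminary evidence suggests "acupuncture may provide a safe and effective alternative treatment option for antenatal depression". The hypotheses that close the Background include that acupuncture, against the attention comparator or usual care, "decreases adverse maternal and infant outcomes".

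**The concern.** The rule applies a causal filter before anything is recorded. Taken as written, an event not judged to come from acupuncture falls outside it even in the acupuncture arm, and nothing equivalent is asked of the other two arms. The prevalence that results has no comparator and depends on attribution. The article does not say who attributes. Practitioners are unblinded (Randomisation and blinding), and the principal investigator is to give the acupuncture and PMR sessions unless unable (Interventions).

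Pregnant women have untoward events in any arm, and without the same collection everywhere the background rate cannot be separated from a treatment effect. The trial's own rationale makes this relevant. It proposes an effect on the oxytocin system and cites studies of acupuncture for preparing, inducing or enhancing labour (Background), and its needling protocol avoids points contraindicated because they augment labour (Interventions). An event such as threatened preterm labour could reasonably be called unrelated by one assessor and related by another. An imbalance between arms in such events could be missed or misattributed.

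**Working it through.** There is no stated figure to reproduce. The check sets the planned data sources against the event types and then sizes what the attributed count could show.

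**1. Which events are covered in which arms**

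| Event type | Source in the article | Same in all arms? |
|---|---|---|
| Worsening mood | Weekly K6; EPDS and DASS-21 | Yes |
| Listed birth and neonatal outcomes | Outcome measures | Yes, no arm restriction |
| Non-psychological events from entry to birth (for example bleeding, threatened preterm labour, antenatal admission) | Safety monitoring rule, if attributed to acupuncture | No |

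Preterm birth itself would show in gestational age at delivery. An antenatal episode that does not end in early delivery is not named among the listed outcomes.

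**2. What the attributed count can show**

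Inputs: rate r = 1.3/1000 = 0.0013 per treatment (Safety monitoring); 8 weekly sessions (Interventions); 32 women per group (Sample size). Sessions are treated as independent.

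- Maximum acupuncture sessions: N = 32 × 8 = 256.
- Expected attributed events: N × r = 256 × 0.0013 = 0.33.
- Chance of none: (1 − r)^N = 0.9987^256 = 0.717; chance of at least one = 0.283.
- If none is seen, the one-sided 95% upper bound per session is 1 − 0.05^(1/256) = 0.0116, about 1.2%. That is 0.0116/0.0013, about 9 times the quoted rate.

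The 256 assumes full attendance by all 32 women. With 25 women (a third of the 75 required before the attrition allowance), N = 25 × 8 = 200, the expected number is 0.26, the chance of none is 0.9987^200 = 0.771, and the upper bound is about 1.5%.

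**3. What an all-arm comparison could show**

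The article gives no background event proportion, so three are assumed. With n = 32 per arm and a two-sided 5% test:

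power = Φ[(d − 1.96 × se0)/se1], where d is the difference in proportions, se0 = √(p̄(1 − p̄) × 2/n) and se1 = √((p1(1 − p1) + p2(1 − p2))/n).

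For 5% against 31.6%: d = 0.266, p̄ = 0.183, se0 = 0.0967, se1 = 0.0908, so power = Φ(0.84) = 0.80.

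| Assumed comparator proportion | Proportion detectable with 80% power |
|---|---|
| 5% | about 32% |
| 10% | about 40% |
| 20% | about 53% |

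Only very large differences would be detected, so the comparison is for description, not testing.

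**The case against.** A reader might infer that no adverse events are collected under PMR or usual care and that the trial cannot compare safety at all. The documents do not support this. Mood deterioration, a central safety signal in a depressed population, is tracked alike in every arm. The maternal-infant outcomes carry no arm restriction, their list is introduced as examples, and fewer adverse maternal and infant outcomes is a stated comparative hypothesis. A partial safety comparison is therefore planned. It would also go too far to call all-cause events the only useful safety data, or to state as fact that the treating practitioner attributes events; the second is a plausible inference only.

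It is also fair to say that a journal article condenses. The article cites protocol version 1.0, a SPIRIT checklist and Good Clinical Practice, and a fuller document may define and collect adverse events in all arms. The sentence does not contain the word 'only'. The word 'safe' in the Abstract describes preliminary evidence and is not a separate safety aim of the trial.

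These points narrow the concern but do not remove it. The Safety monitoring section is not silent: it states a scope, and that scope is causal and tied to one intervention. Followed as written, it leaves non-psychological events between entry and birth without like-for-like capture. The objection that 32 per arm is too few for a powered safety comparison also stands, and it limits what the fix can claim.

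**Conclusion.** The concern holds in limited form. The one adverse-event rule in the article depends on attribution to acupuncture and yields a prevalence without a comparator. Events such as bleeding, threatened preterm labour or antenatal admission are therefore not captured alike across the three arms, and their capture rests on a causal judgement in a trial with unblinded practitioners. The K6, EPDS, DASS-21 and maternal-infant data allow part of a safety comparison but do not name these events.

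The attributed count adds little. Seeing no event is the likely result (72% to 77% for 256 to 200 sessions), and it would still be compatible with a per-session rate of about 1.2% to 1.5%. These figures rest on the article's quoted rate and on independent sessions. The conclusion about scope does not depend on them; it rests on the stated rule and assumes that no fuller document widens it. This should be corrected, but it does not threaten the primary analysis.

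**What to change.** Replace the adverse-event sentence in Safety monitoring with: *All adverse events and serious adverse events, regardless of attribution, will be recorded by the same question in all three arms at the weekly K6 contact and at 6 weeks post-natally, and reported descriptively by arm alongside the K6 and maternal-infant data; relatedness will be recorded separately.* If the full protocol already provides for this, the article's sentence should be aligned with it.

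The cost is one question at contacts that already take place in every arm, one table by arm and a little data entry. No treatment changes. Recruitment was under way when the article was published, so women who have already completed the intervention will lack the weekly data. The report should state how many women this affects in each arm and from what date the question was used.

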### Interventions

In the first session, a full case history will be taken and a traditional Chinese medicine (TCM) and meridian therapy diagnosis will be made. This will also occur for the usual care group upon trial entry. The intervention groups will then receive weekly 1-h treatments over the 8-week period. At the end of each session, 5 minutes will be spent gaining feedback regarding the session. Treatments will be conducted in the antenatal clinics of either hospital or at the NICM.

The acupuncture protocol draws upon TCM theoretical foundations and treatment strategies as well as some generalisable traditional East Asian medicine approaches. The three-stage semi-standardised flexible process (Fig. 2) incorporates a ‘root’- and ‘branch’-style treatment [113, 114] as well as auricular acupuncture. The ‘root’ treatment (step 1) aims to provide a fundamental harmonisation via the extraordinary meridian system, while the ‘branch’ treatment (step 2) focuses on remaining disruptions in a more symptomatic way [114–116]. Use of the extraordinary meridian system as a root-style approach has been suggested to facilitate a longer-lasting, more penetrating effect [114, 116] by virtue of this system’s ability to regulate the ‘qi’ of all of the yin-and-yang channels [117], access and distribute ‘pre-heaven essence’ throughout the entire body [116, 118] and affect a person at a constitutional level, due to its embryological roots [116, 118, 119]. Specific functions relevant to depression include influences to the marrow [116], brain, spinal chord, hypothalamic–pituitary–ovarian axis [120], circulatory, hepatic, biliary [121] and endocrine [118] systems. Pathology within this system is thought to manifest in the mind or ‘shen’ [118], and as such treatment is recommended for mental and/or emotional problems [118, 120] as well as cases of mixed pattern complexity involving multiple meridians [118]. In step 1, diagnosis of the most disharmonious extraordinary meridian pair will be made on the basis of the presence of relevant mood disturbance symptomology [116] in combination with disease indicating palpatory findings along involved channel trajectories [117–119]. If uncertainty remains regarding which of the 2 points of the meridian pair will be the master point (MP), each point will be tested with acupressure to see which one provides the greatest meridian improvement. After identification, the gender-appropriate MP and coupled point (CP) (Table 1) will be unilaterally needled with the meridian flow to ensure that the areas traversed by both vessels are influenced [118]. This method was recommended by Maciocia in 2006 [118] for problems of the head and internal organs, weakened body condition and anxiety. It is also suitable for pregnant women in side-lying position. Japanese-style practitioners typically apply polarity devices to the MP and CP to remedy detected pathologies in the extraordinary vessel system [119, 122]. However, for the purposes of generalisability, polarity in this case will be achieved by side of sex-directed unilateral needling and reverse-order withdrawal [116]. Whilst needles are retained for 10–15 minutes, further diagnosis will be performed by palpation and questioning. As many of the symptoms of depression correspond to TCM ‘yang deficiency’ such as lethargy, reduced libido and lack of motivation [116], it has been theorised that disruption to the major yang channel, the extraordinary meridian governor vessel (GV) that traverses the middle of the back and head, is implicated in depression [123]. Treatment recommended by Wang and Zhang in 2010 [123] is the needling of the most painful or obstructed points along this channel or on the slightly adjacent Huato Jia Ji (HJJ) points, serving a dual main channel and extraordinary vessel function [118]. Step 2a will involve needling of the two points located in this way, in combination with either GV 20 (bai hui) [124] + GV 16 (feng fu) [124], the ‘Sea of Marrow’, indicated for mania, suicidal tendencies and calming the spirit; or ‘Shi Shen Cong 4-4 Alert spirits’, indicated for mania, depression, insomnia and calming of the spirit [117]. Selection in either case will be based upon palpation tenderness and/or symptom differentiation. Whilst these needles are retained, step 2b will involve the needling of two to six additional tender points, if required, according to numerous theoretical possibilities (see Tables 2 and 3) such as the ability to clear reflex areas, for a combined total time of 15–20 minutes. A step 2b example is the association between depression and inflammation [125] viewed as ‘heat’ in TCM; hence, if detected at a ‘fire’ point on a meridian trajectory, a remedying treatment involving the needling of ‘water’ and ‘metal’ points’ [116] to extinguish the ‘fire’, may be selected. Step 3 will then comprise two stainless steel pellets (Helio Supply Co., San Jose, CA, USA) being placed on appropriate points in the ear (Table 4) to extend the treatment effect [122] for an additional 5 days. Lifestyle and dietary advice, contraindicated labour augmentation points [126] and painful needling techniques will be avoided [127]. Needles will be inserted into the most sensitive area within the specified point location or ‘live’ point [100] to a depth enabling retention (2–6 mm), either perpendicularly (even technique) or obliquely with the meridian flow (tonification) and taped in place to allow for adjustment of position during the session. AcuGlide (Helio Supply Co.) single-use stainless steel needles 0.16 mm × 30 mm will be used predominantly, with 0.14-mm or 0.12-mm needles selected for tenderer locations.

**Fig. 2 Fig2:**
[figure not shown]
Acupuncture treatment flowchart. *CP* coupled points, *GV* governor vessel, *HJJ* Huato Jia Ji, *LHS* left-hand side, *MP* master points, *RHS* right-hand side

**Table 1 Tab1:** Master and coupled point pairings of the eight extra vessels

Extraordinary meridian	Master point (right)	Couple point (left)
Ren Mai – Directing Vessel	Lung (LU) 7 (lie que)^a^	Kidney (KD) 6
Yin Qiao Mai –Yin Heel Vessel	Kidney (KD) 6 (zhao hai)	Lung (LU) 7
Chong Mai – Penetrating Vessel	Spleen (SP) 4 (gong sun)	Pericardium (PC) 6
Yin Wei Mai – Yin Linking Vessel	Pericardium (PC) 6 (nei guan)	Spleen (SP) 4
Dai Mai – Girdle Vessel	Gallbladder (GB) 41(zu lin qi)	Triple burner (TB) 5
Yang Wei Mai – Yang Linking Vessel	Triple burner (TB) 5 (wai guan)	Gallbladder (GB) 41
Du Mai – Governing Vessel	Small intestine (SI) 3 (hou xi)	Bladder (BL) 62
Yang Qiao Mai – Yang Heel Vessel	Bladder (BL) 62 (shen mai)	Small intestine (SI) 3

The eight extra vessels are described by Maciocia [116].

^a^From Ellis et al. [124]

**Table 2 Tab2:** Step 3: Additional relevant point possibilities

Symptom and theoretical foundation	Points
Severe Yang deficiency^a^	GV 4 (ming men)^b^ and GV 14 (da zhui) or GV 4 and TB 4 (yang chi)
Anxiety + pressure pain at PC 8 (lao gong) or SP 2 (da du) – pericardium or spleen metal and water points^c,d^	PC 3 (qu ze) and 5 (jian shu) or SP 5 (shang qiu) and 9 (yin ling quan)
Anxiety + pressure pain at CV 12 (zhong wan) – points of the heart shu area^d^	T5/HJJ/BL 15 (xin shu)/BL 44 (shen tang)/BL 49 (yi she)
Anxiety + pressure pain at CV 17 (dan zhong)^d^	GB 13 (ben shen)
Depression/mental disturbance – ‘blood stagnation in the head’^c^	First – SP 9 (yu ling quan) second – PC 8 or PC 6 or PC 3 + 5
Depression due to adrenal exhaustion^c,d^	KD 6 and lateral to LU 5 (chi ze) or KD 6 and KD 27 (shu fu)
Depression and sphenoid bone disturbance – pressure pain at GB 4 (han yan)/5 (xuan lu)/6 (xuan li)^d^	Needle most tender
Depression and sphenoid bone disturbance – pressure pain TB 17 (yi feng) and TMJ^c^	KD 9 (zhu bin) and 27 and above TB 9 (si du) side of pain
Depression and pituitary disturbance^c^	SI 3, SI 13 (qu yuan), BL 2 (zan zhu) and 1 cun above BL 10 (tian zhu)
Melancholic depression^d^ – if positive for pressure pain/pulsation at CV 9 (shui fen)^d^	ST 24 (hua rou men) RHS, LU 9 (tai yuan)
Depression – LR 2 (xing jian) pressure pain – water and metal points^c^	LR 4 (zhong feng) and 8 (qu quan)
Depression – pressure pain LR organ region and LR 14 (qi men)^c^	LHS – lateral to LU 5 (chi ze), LR 4 and LR 14 RHS
Chronic depression and weakened immune system – pressure pain R ST 26 (wai ling)/27 (da ju ) and TB 16 (tian you)^c^	Tender point around LI 10 (shou san li)/11 (qu chi)
Subclinical underactive thyroid gland^c^	Eustachian, TB 4, KD 9/10 (yin gu), BL 43 (gao huang shu), HJJ C6/7
Inflammation – TCM meridian heat signs – metal and water points to extinguish^e^	Meridian-dependent
Mental health relevant points – selected by point function and palpation tenderness	See Table 3 for options

*BL* bladder meridian, *CV* conception vessel, *GB* gallbladder meridian, *GV* governor vessel, *HJJ* Huato Jia Ji, *KD* kidney meridian, *LHS* left-hand side, *LU* lung meridian, *LI* large intestine meridian, *LR* liver meridian, *PC* pericardium meridian, *SP* spleen meridian, *ST* stomach meridian, *RHS* right-hand side, *SI* small intestine meridian, *TB* triple burner meridian, *TCM* traditional Chinese medicine

^a^Maciocia [116]

^b^Ellis et al. [124]

^c^Matsumoto and Euler [134]

^d^Matsumoto and Euler [135]

^e^Kendall-Tackett [125]

**Table 3 Tab3:** Possible points and point combinations useful for the treatment of antenatal depression

Points	Indications/Symptom alleviation
ST 40 (feng long)^a^	Spleen deficiency, damp and phlegm misting – heaviness, confusion, metal disturbance
ST 23 (tai yi)	Transforms phlegm and calms the spirit – mania, depression, agitation
ST 24 (hua rou men)	Transforms phlegm and calms the spirit – mania, depression
LR 3 (tai chong)	LR Qi stagnation, irritability, feeling of oppression
BL 42(po hu)	Breathing difficulties, grief, worry, sadness
BL 43	Increases spleen yang and lung function, calms the spirit, resolves phlegm
BL 44	Calming and mental clarity
BL 47 (hun men)	Enables clear and positive life planning and decision making
BL 47 and BL 52(zhi shi)	Together adds stability to plans and decisions, also for LR Qi stasis attack on lungs
BL 49	Obsessive thinking, improved memory and concentration
BL 52	Willpower, determination, initiation
BL 52 and BL 42	Willpower and emotional release
BL 52 and BL 44	Willpower, calming, anxiety, depression, mental restlessness and insomnia
BL 52 and BL 47	Willpower and life direction, chronic depression with mental exhaustion, apathy and despondency
BL 52 and BL 49	Willpower, obsessive thoughts, worry and confusion
BL 10 (tian zhu)	Calms the spirit
BL 17 (ge shu)	Mania, depression
GV 18 (qiang jian)	Liver blood deficiency, calming, mental restlessness, agitation, confusion, obsessive thinking
GV 19(hou ding)	Willpower, calming, anxiety, mental restlessness, kidney yin deficiency heat
GV 19 and CV 15 (jiu wei)	Calming, insomnia, mental restlessness
GV 20 (bai hui)	Lifts mood, aids memory and concentration
GV 21(qian ding)	Anxiety, insomnia, depression
GV 24 (shen ting)	Clears the mind
GV 24 and GB 13	Calming, anxiety, mental restlessness due to LR causes
CV 14 (ju que)	Transforms phlegm and calms the spirit
CV 15	Calming, chest oppression
GB 9 (tian chong)	Calms the spirit and pacifies fright
GB 12(wang gu)	Mania, agitation of the heart and insomnia
GB 13	Calming, mental clarity, severe anxiety and mental restlessness resulting from LR disharmony
GB 13 and GV 24	Same as for GB 13 with enhanced calming effect
GB 13 and HT 7 (shen men)	Calming, severe anxiety due to heart disharmony
GB 15 (tou lin qi)	Calms the spirit, reduces emotional fluctuations and obsessive thinking
GB 17 (zheng ying)	Calms the spirit, aids memory and concentration
GB 18 (cheng ling)	Stops obsessive thoughts, strengthens the function of the lungs and clears the nose
GB 40 (qiu xu)	Willpower, difficulty making decisions
HT 7	Calms the spirit, heart blood and yin deficiency
HT 6 (tong li)	Calms the spirit, repletion patterns with vacuity heat
HT 8 (shao fu)	Calms the spirit – agitation, fright palpitations, depleted sadness and worry
HT 9 (shao chong)	Calms the spirit – mania, depression, severe mental restlessness, anxiety, insomnia
HT 5 (tong li)	Calms the spirit – depressive disorder
PC 4 (xi men)	Calms the spirit – agitation, insomnia, melancholy, spirit qi deficiency
HT 7 and PC 6	Calms the spirit – shen disturbance, anxiety, mental restlessness
KD 7 ( fu liu) and HT 6 (yin xi)	Calms the spirit – heart and kidney not communicating, agitation, insomnia, anxiety
PC 5	Settles and calms the spirit – mania and agitation
PC 7 (da ling)	Calms the spirit – depressive disorder
PC 6	Calms the spirit, lifts mood – qi stagnation emotional problems, anger, resentment and frustration
PC 6 and SP 4	Opens yin wei mai, nourishes blood, relaxes the chest, calms the spirit
PC 6 and LR 3	Resolves qi stasis from repressed anger
PC 6 and GV 20	Lifts the mood, relieves depression
PC 6 and GV 26 (shu gou)	Lifts the mood, opens heart orifices, relieves depression
SI 7 (zhi zheng)	Calms the spirit – mania, depression, anxiety, sadness, fear and fright
KD 9 (zhu bin)	Clears the heart and transforms phlegm – mental restlessness, mania, depressive disorders
SI 7 and HT 3 (shao hai)	Chronic anxiety, depression, fear or emotional distress
LI 5 (yang xi)	Calms the spirit – mania, depression

*BL* bladder meridian, *CV* conception vessel, *GB* gallbladder meridian, *GV* governor vessel, *HJJ* Huato Jia Ji, *KD* kidney meridian, *LHS* left-hand side, *LU* lung meridian, *LI* large intestine meridian, *LR* liver meridian, *PC* pericardium meridian, *SP* spleen meridian, *ST* stomach meridian, *RHS* right-hand side, *SI* small intestine meridian

Information is from MacPherson and Schroer [98]; Schnyer and Allen [99]; Deadman et al. [117]; Matsumoto and Euler [136]; and Rogers and Rogers [147]

^a^Ellis et al. [124]

**Table 4 Tab4:** Auricular point possibilities

Name	Function
Point Zero	Homeostasis, will power
Shen men	Pain, tension, anxiety and depression
Sympathetic tone	Sympathetic nervous system balance
Cheerfulness	Relieves depression
Excitement	Relieves hypersomnia and depression
Master cerebral point	Anxiety, worry, obsessive compulsive disorders, psychosomatic disorders and chronic pain
Master oscillation point	Balances left and right cerebral hemispheres
Sleep disorders 1	Relieves insomnia, nervousness
Sleep disorders 2	Relieves insomnia, sleep difficulties, nervous dreams
Depression	Relieves depression
Endocrine	Hormone imbalance
Nervousness	Relieves nervousness
Adrenal	Adrenal fatigue/disturbance
Thyroid 1–4	Thyroid function disturbance
Marvellous/wonderful	Lifts mood
Aggression	Alleviates aggression/irritability
Mania	Relieves manic symptomology
Insomnia	For sleep disturbance
Vitality	For lethargy and despondency
Stress control	Relieves stress
Tranquilizer	Calms the spirit
Guilt	Alleviates feeling of guilt
Overwhelmed	Stress, emotional paralysis, despondency
Burdened	Emotional paralysis, despondency, overwhelm

Adapted from several different Chinese medicine–based auricular maps obtained from the internet: https://www.google.com.au/search?q=chinese+auricular+ear+acupuncture+chart&biw=1140&bih=610&tbm=isch&tbo=u&source=univ&sa=X&ved=0ahUKEwjO6ofuuebKAhXEUZQKHR-UAAkQsAQIGg.

In our examination of recent reviews of acupuncture as a treatment for depression [35, 36, 128–130], we identified three main treatment approaches previously used: (1) fixed points for mood disturbance alleviation, (2) fixed points of this function in combination with additional points selected according to TCM pattern differentiation and (3) flexible point selection based entirely upon TCM pattern discrimination. Variations included diagnosis of disrupted extraordinary vessels Chong and Ren in one study [131], an abdominal points focus in another [132] and scalp acupuncture in a third [133]. Many studies included auricular acupuncture as well as multiple points along the extraordinary GV meridian. Two research groups developed flexible manualised protocols based on pattern differentiation [98, 99], one of which also provided modifications for pregnancy [99]. Both have been drawn upon for therapeutic possibilities presented in Tables 2 and 3, in combination with those suggested by Matsumoto and Euler in 2002 [134] and 2008 [135], such as for the alleviation of commonly observed LR Qi stagnation [98]. It is theorised that the approach of extraordinary meridian treatment in combination with mental disturbance–oriented pattern differentiation and symptom alleviation may provide additional therapeutic outcomes. In 2009, Finston [136] used a similar strategy in patients with severe mental disorders and reported significant reduction or alleviation of psychotic symptoms [136].

The PMR comparator has been adapted from previous research [137] to achieve overall body relaxation in all sessions with an additional weekly focus as follows: introduction (week 1); lower legs and knees (week 2); upper legs and buttocks (week 3); lower back and pelvic floor (week 4); upper back and chest (week 5); arms and shoulders (week 6); head, face and neck (week 7); and integration (week 8). Participants, whilst lying in a comfortable position, will be guided through the PMR in a one-to-one format. A participant who is unable to attend will be offered either a recording- or telephone-based session for home administration.

All groups will continue standard antenatal care, which may include medication and or counselling as well as antenatal classes. In compensation for not receiving treatment, the usual care group will be offered four acupuncture sessions after collection of final data at 6 weeks post-natally.

The principal investigator of this trial ([name]) has 14 years of full-time clinical experience and will conduct all acupuncture sessions, unless unable, in which case a backup acupuncturist with 14 years of part-time clinical experience will be employed. Both practitioners have bachelor’s degrees in acupuncture and are registered with the Chinese Medicine Board of Australia and the Australian Acupuncture and Chinese Medicine Association. The principal investigator will also conduct all PMR sessions, unless unable, in which case a backup associate researcher will be employed.

